## Exclusion Criteria

Participants who meet any of the following exclusion criteria are not eligible for the study.

- Active untreated syphilis
- Current uncontrolled hypertension (blood pressure > 160/100 mmHg)
- Mutually monogamous (members of couple engage in sexual activities only with each other, excluding all others) relationship for > one year with a known HIV antibody negative partner
- History of chronic renal disease, known osteoporosis, osteomalacia, or osteopenia
- Bone mineral density Z score < -2.5 at the total spine, total hip or femoral neck on screening (done at SFDPH only), or current treatment for secondary causes of low bone mineral density.
- Current or expected participation in other longitudinal HIV behavioral or biomedical research study
- Current HIV antiretroviral use
- Receiving or planning to receive on-going therapy with any of the following:
- Nephrotoxic agents
- aminoglycoside antibiotics
- intravenous amphotericin B
- cidofovir
- cisplatin
- foscarnet
- intravenous pentamidine
- other agents with significant nephrotoxic potential
- Probenecid
- Metformin
- Experimental or investigational agents
- Previous or expected requirements for the administration of immunosuppressive/ immunomodulatory therapy (e.g. chronic systemic corticosteroids, interferon, interleukins, chemotherapy, radiation).
- Evidence of a gastrointestinal malabsorption syndrome or chronic nausea or vomiting which may confer an inability to receive an orally administered medication.
- Current alcohol or substance abuse judged by the investigator to potentially interfere with participant compliance.
- Imminently life-threatening medical conditions (malignancy, immunosuppressive disease [e.g. lymphoma]), or other serious disease or conditions (e.g. cardiovascular, renal, diabetes) within the last 5 years or that are unstable and/or require chronic medication that would, in the investigator’s judgment, impede compliance with study requirements and complicate the interpretation of adverse events
- Expected to be non-compliant with study visits or planning to move within 24 months to an area where the study will not be conducted
- Any other clinical or social condition, prior therapy, occupation, or other responsibility, that, in the opinion of the investigator, would interfere with, or serve as a contraindication to study participation or compliance with the dosing requirements.

# TREATMENT PLAN AND STUDY PRODUCT

## Treatment Plan

Participants will be assigned a participant number at the time of screening consent. Once eligibility has been confirmed, the site will be given a specific numeric identifier that corresponds to the product assignment. All screening and baseline tests and procedures must be completed prior to the receipt of the first dose of study product. Initiation of treatment with study product must take place within 24 hours after product dispensation.

## Randomization

Participants will be randomly assigned to one of the four arms: immediate study product receipt (TDF or placebo) or delayed study product receipt (TDF or placebo) in a 1:1:1:1 ratio. A CDC statistician will develop the allocation sequence using a permuted blocks randomization scheme. In a block of 8 study numbers, 2 assignments will be to immediate TDF, 2 to immediate placebo, 2 to delayed TDF, and 2 to delayed placebo. Randomization codes will be provided to Gilead Sciences, Inc., and study bottles will be labeled and filled with TDF or placebo using these codes and shipped to the appropriate site. Participants will be randomized to a group only after they have consented to participate and they have met the eligibility requirements for the study. Randomization will be stratified by study site. The list of treatment assignments and the assignment codes will be known only to the statistician and designated individual at Gilead Sciences, Inc., and only CDC will have access to the list of treatment assignments should the need for this information arise.

Group assignments will be concealed in sequentially numbered, sealed envelopes that will be distributed to each site by CDC and maintained in a secure location. After a participant has been properly enrolled in the study, a designated study staff member will obtain the next randomization envelope in sequence and be provided the information indicating the participant’s assignment to a delayed or immediate arm and the randomization number (bottle identification number) assigned.

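### A single block size of 8, printed in the protocol and combined with open immediate/delayed assignment, lets a site foresee about one timing assignment in five

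*Protocol*

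**What the plan says.** Protocol Section 5.2 (Randomization) allocates men to immediate or "delayed study product receipt (TDF or placebo) in a 1:1:1:1 ratio". A CDC statistician is to "develop the allocation sequence using a permuted blocks randomization scheme", and the composition is printed: "In a block of 8 study numbers, 2 assignments will be to immediate TDF, 2 to immediate placebo", with 2 each to delayed TDF and delayed placebo. No other block size is mentioned. "Randomization will be stratified by study site", so each site works through its own blocks.

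The concealment device is described as follows: "Group assignments will be concealed in sequentially numbered, sealed envelopes that will be distributed to each site by CDC". After enrollment, "a designated study staff member will obtain the next randomization envelope in sequence" and learns both the timing arm and the bottle number. The blind in Section 5.2.1 covers TDF against placebo only. Timing cannot be blinded, because Section 3 gives the delayed arms no product for nine months.

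Section 11.1 places the protocol in each investigator's study file. Section 10.6 makes immediate against delayed over the first nine months the main behavioral safety analysis, which serves one of the two primary endpoints in Section 10.2.1.

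**The concern.** Sealed envelopes hide the next assignment only if it cannot be inferred from those already opened. Here the block size is in the site's own file and the timing arm of every earlier man at that site is known to staff. Counting what remains in the block is enough to predict, sometimes with certainty, whether the next man will start pills now or wait.

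Staff also have some influence over who comes next. Section 4.4 contains judgment-based exclusions, such as "Expected to be non-compliant with study visits" and a general one resting on the investigator's opinion. Section 6.3 allows enrollment at any point within 45 days of screening.

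If men who are keener on pills, or at different behavioral risk, were brought in when a particular timing arm was due, the two timing groups would differ at entry. The behavioral comparison is self-reported and open as to pill or no pill, so unpredictable allocation is its chief protection.

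**Working it through.** **Inputs**
- Block of 8 with 2 per arm, 1:1:1:1, stratified by site: Section 5.2.
- Total 400: Section 10.3.
- Behavioral effect of interest 12 percentage points, with 28% or more in the delayed group: Section 10.6.

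**Step 1. The plan's own figure.** 8 × 1/4 = 2 per arm, so 4 immediate and 4 delayed per block. The composition agrees with the ratio; no stated number is wrong. 400/8 = 50 full blocks.

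**Step 2. Assignments known with certainty.** There are C(8,4) = 70 equally likely immediate/delayed orders. The last k assignments are all known in advance when they are all alike, which has probability 2·C(8−k,4)/70:
- k = 1: 2·35/70 = 100%
- k = 2: 2·15/70 = 43%
- k = 3: 2·5/70 = 14%
- k = 4: 2·1/70 = 3%

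The sum is 1 + 0.429 + 0.143 + 0.029 = 1.6 per block. This matches the closed form 2b/(b+1) = 8/5 with b = 4. 1.6/8 = 20%, and 0.20 × 400 = 80 men.

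**Step 3. Best-guess accuracy.** Always naming the timing arm with more places left gives b + 2^(2b−1)/C(2b,b) − 1/2 = 4 + 128/70 − 0.5 = 5.33 correct of 8, or 66.6%. Full enumeration of the 70 orders gives the same value.

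**Step 4. What steering could do (illustration; the risk differences are assumptions).** Suppose the baseline probability of a yes response differs by d between men entered when immediate is guessed and men entered when delayed is guessed. The expected imbalance between the timing groups is d × (2 × 0.666 − 1) = 0.332d.
- d = 5 points: 1.7 points
- d = 10 points: 3.3 points
- d = 20 points: 6.6 points

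These figures assume steering at every enrollment. If only the certain assignments were used, d = 10 gives 0.20 × 10 = 2.0 points. The study is powered for 12.

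**Step 5. Effect of mixed block sizes.** This was simulated with 134 men per site (about 400/3, an assumed equal split over three sites). The guesser makes optimal use of past assignments and knows the possible sizes but not where blocks begin.

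| Block sizes | Known with certainty | Best guess correct |
|---|---|---|
| 8 only | 19.1% | 66.5% |
| 4/8 | 7.4% | 67.8% |
| 4/8/12 | 2.9% | 65.9% |
| 8/12/16 | 1.6% | 63.9% |

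The first row is just under 20% because 134 is not a multiple of 8 and the last block is cut short. The candidate sizes are my choice.

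**The case against.** Section 5.2 has real safeguards: consent and confirmed eligibility come first, envelopes are sealed, numbered and stored securely, and one is taken only after the man is enrolled. These prevent a change of mind once an envelope is open. They do not prevent inference from envelopes opened earlier at the same site.

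Much of eligibility is laboratory based (Section 4.3), which narrows the room for steering without closing it. Risk behavior is also recorded by ACASI at enrollment (Sections 6.3 and 8.6), so a measured imbalance could be detected and adjusted for. That stands, although it does not cover unmeasured differences.

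A reader might infer that the behavioral comparison is biased. The documents do not support that. Bias needs staff who keep a tally, want to steer, and steer on something related to risk behavior, and nothing in the protocol shows such conduct. Section 10.3 does list participation, especially in the delayed arms, among its design considerations. That makes a motive conceivable and no more.

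A reader might also infer that the randomized comparison of TDF with placebo is exposed. It is not: opening an envelope reveals timing and a coded bottle number, not the product.

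Finally, it is fair to object that mixed blocks hardly change best-guess accuracy. That is correct, and the benefit should not be described otherwise.

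**Conclusion.** The point holds as a design weakness, not as an error or contradiction. With one disclosed block size of 8 within site and open timing, 20% of timing assignments (about 80 of 400) can be known with certainty beforehand, and 66.6% can be guessed correctly. This creates an avoidable risk of selection bias in a primary comparison. On the illustrative assumptions the resulting imbalance would be about 2 to 7 points, against the 12 points of interest.

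The predictability figures rest on three readings: 8 is the only block size, since none other is stated; sites read the protocol they hold; and blocks are filled completely. The bias figures rest in addition on assumed steering that the documents do not show.

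**What to change.** For envelopes not yet issued, generate the remaining sequence within site from randomly mixed block sizes that are multiples of 4. Larger sizes are preferable: 8/12/16, or 4/8/12. A 4/8 mix is less useful, since it leaves 7.4% certain and slightly raises guessing accuracy. Remove the block size and composition from Section 5.2 and keep them in a restricted document held by the CDC statistician. Mixing is needed as well as removal, because sites that already hold the protocol have seen the number.

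The gain is mainly the loss of certain knowledge, from about 20% to about 2-3%. Best-guess accuracy falls only to about 64-66% if the set of sizes becomes known.

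The cost is slightly looser balance within site and some supply work. Bottles are filled and labeled from the randomization codes (Section 5.2) and kits are packed differently for the two timing arms (Section 5.3.1), so the new sequence must be matched to existing coded stock, with care against assignment errors. No visits or participants are added. Assignments already made are unaffected. Section 6.5 refers to men already enrolled, and the protocol does not say how many envelopes remain, so the reach of the change is unknown.

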### Blinding

TDF and placebo will be provided to the study sites in identical bottles labeled only with the participant ID number. If HIV testing reveals confirmed HIV-1 infection, infected participants will be informed about their infection and asked to permanently discontinue study product, and continue with Part B of the study. All HIV-infected participants will receive HIV genotypic and phenotypic resistance testing at diagnosis, and they (and their health care providers if they so request) will receive these results. Since unblinding is not necessary for future clinical management, the participant, study site, and staff will remain blinded as to their treatment assignment group until the study is closed and the database locked.

CDC will be notified of all serious adverse events. Unblinding will occur only in urgent situations where the need for the knowledge of product receipt is shown to be critical to the participant’s care. The unblinding request with the rationale for the request should be provided to CDC and the medical monitor.

### Minimizing unblinding related to adverse events

The study design requires double-blind administration of study product (TDF or placebo). In previous studies of TDF, there were no adverse events exclusively associated with the active study or that required knowledge of the product assignment to administer care. Thus, the observation of any particular adverse event should not require unblinding of either researcher or participant.

### Minimizing potential for self-unblinding

Considerable bias could be introduced if participants were unblinded and risk behavior changed differentially in the treatment groups. For example, if participants have their blood or study product tested outside of the study, they may be able to determine if they received TDF or placebo. If TDF recipients assumed that they were protected and increased their risk-taking behavior while placebo recipients’ risk behavior was unchanged, the resulting increase in infections among TDF recipients could offset any true protection offered by TDF and impede the ability to accurately assess safety.

To minimize the risk of bias related to ascertainment of product assignment, the following actions will be taken. First, all participants will be counseled not to assume any protection from study product and to avoid high risk behaviors. Second, at enrollment, 6 month intervals, and study conclusion, participants will be asked about their perceived treatment assignment. Third, at enrollment and at subsequent 3 month intervals during the study, participants will self-report their risk-taking behavior by ACASI and receive HIV testing and counseling regarding risk behavior reduction. The information collected from the risk assessments will be reviewed at each safety review and at the conclusion of the study to assess the comparability of self-reported risk behaviors for the initial 9 months between the delayed and immediate treatment arms and before and after treatment initiation for the delayed treatment arms.

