# STUDY DESIGN

This protocol describes a randomized, double-blind, placebo-controlled three-site study to evaluate the safety and tolerability of daily oral TDF among HIV-1 negative MSM.

Four hundred healthy, HIV‑1‑negative MSM will be randomized to one of four treatment arms:

Group 1: TDF 300 mg po QD

Group 2: Placebo po QD

Group 3: No study product for 9 months, followed by TDF 300 mg po QD

Group 4: No study product for 9 months, followed by placebo po QD

Groups 1 and 2 will be referred to as the immediate treatment arms and will receive study product for the entire 24 months of the study. Groups 3 and 4 will be referred to as the delayed treatment arms, and will receive study product starting at 9 months and ending at 24 months, for a total duration of 15 months on study product. For the purposes of this study, a month is considered 30 days. Participants will be stratified by enrollment site.

Participants will be monitored for clinical safety using periodic physical examinations, adverse event reporting, and serial laboratory testing. Given the uncertainty regarding the clinical significance of whole-body duel-energy x-ray absorptiometry [DEXA] findings and their lack of correlation with other clinical data (e.g. fractures), SFDPH site participants will receive DEXA scans at screening and two follow-up visits (at 12 and 24 months in the immediate arm, at 9 and 24 months in the delayed arm), and at the time of study discontinuation, if at least 6 months has passed since the previous scan. Behavioral safety will be primarily assessed by comparing reported risk behaviors between the immediate (pill-groups 1 and 2) and delayed (no pill-groups 3 and 4) treatment arms and will be evaluated by the use of periodic risk behavior assessments via audio computer-assisted self interview (ACASI) and regular laboratory testing for HIV and sexually transmitted infections (STI) including syphilis, *Neisseria gonorrhoeae* (GC), and Chlamydia trachomatis (CT). Additionally, measurements of adherence will be evaluated to determine product acceptability.

Study Schema

R

A

N

D

O

M

I

Z

E

Daily TDF

Daily Placebo

No treatment for 9 months, then daily TDF

No treatment for 9 months, then daily Placebo

Site B

Site A

Site C

Anticipated Timeline

Months

|  | 0-6 | | 7-12 | | | | 13-18 | | | 19-24 | | 25-30 | 31-36 | | 37-42 | |
| --- | --- | --- | --- | --- | --- | --- | --- | --- | --- | --- | --- | --- | --- | --- | --- | --- |

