## Safety Analyses for Behavioral Outcomes

Data will be collected on HIV risk behaviors at enrollment and 3-month intervals throughout the study to assess the behavioral safety of study product use. The main behavioral safety analysis will compare the overall level of selected behaviors in the immediate and delayed treatment arms over the first nine months of the study. Statistical analyses for dichotomous (yes/no) responses will account for the within-individual correlation using longitudinal binary regression models. The study will have good power (>80%) to detect differences in the probability of a yes response between the groups of 12% or more assuming that the probability of a yes response in the delayed group is 28% or greater. All analyses will account for within-individual correlation using longitudinal models for continuous variables (e.g. Poisson outcomes). Subsequent analyses will examine whether there is a trend in the difference of a yes response between the two groups over time and trends in the probability of a yes-response within both the TDF and placebo groups while on study product. This last analysis will also be examined in relation to an individual’s perception that they have been randomized to a TDF group.

In all analyses, study drop-outs will be evaluated to assess their comparability to either a) all others still on study (missing completely at random) or b) to others still on study within their site by study group (missing at random).

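### The behavior review meant to guard against self-unblinding pools TDF with placebo, although the bias it names is a rise in risk behavior among TDF recipients only

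*Protocol*

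**What the plan says.** The subsection on minimizing the potential for self-unblinding, under Section 5.2, describes the bias as a contrast between products: "If TDF recipients assumed that they were protected and increased their risk-taking behavior while placebo recipients’ risk behavior was unchanged". It lists three actions: counseling, asking men at intervals which product they think they have, and three-monthly ACASI with HIV testing and counseling. It then says what the risk data will be used for at each safety review and at the end: "to assess the comparability of self-reported risk behaviors for the initial 9 months between the delayed and immediate treatment arms", and a second comparison "before and after treatment initiation for the delayed treatment arms".

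Section 3 shows that the first comparison pools the products: "comparing reported risk behaviors between the immediate (pill-groups 1 and 2) and delayed (no pill-groups 3 and 4) treatment arms". Section 10.6 makes the same contrast the main behavioral analysis: "The main behavioral safety analysis will compare the overall level of selected behaviors in the immediate and delayed treatment arms", over the first nine months. It then adds "trends in the probability of a yes-response within both the TDF and placebo groups while on study product", and continues: "This last analysis will also be examined in relation to an individual’s perception that they have been randomized to a TDF group".

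Three other places speak in general terms. Section 10.1 promises a comparison of behavioral safety data among the study arms. Section 10.2.1 defines the behavioral endpoint as change in each treatment group. The end of Section 10.5 says safety analyses will be adjusted for site and for immediate or delayed group, and that modification of outcome-treatment relationships will be explored. For adherence, by contrast, Section 10.7 names TDF versus placebo on product as the major comparison.

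**The concern.** The comparisons do not match the bias they follow. If men on TDF learn their assignment and change behavior while men on placebo do not, the change lies between TDF and placebo among men taking tablets. Neither comparison in the self-unblinding subsection looks there.

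- **Immediate versus delayed.** During the first nine months the delayed men know they have no tablets, so this contrast is open by design. It measures the effect of taking any tablet, and only half of the immediate men are on TDF.
- **Before versus after in the delayed arms.** This is not a randomized contrast. It is mixed with time on study and repeated counseling, and again only half the men start TDF.

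The review could therefore look clean while men on TDF behave differently. It could also show a difference that nobody can attribute to a failure of the blind. The protocol itself says that such a bias could offset true protection and impede the safety assessment.

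**Working it through.** **Inputs from the protocol**
- 400 men allocated 1:1:1:1, so 100 per arm and 200 immediate versus 200 delayed (Section 10.3).
- 28% in the delayed group and a difference of 12 points (Section 10.6).
- ACASI at months 3, 6 and 9: three visits in the first nine months (Section 6.8). There are five quarterly visits in the 15 months on product that all arms share.
- Loss to follow-up of 10-20% (Section 10.3).

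**Assumptions**
- Within-man correlation r = 0.5. Section 10.7 gives this for adherence only, so 0.3 to 0.7 is shown as a range.
- Two-sided 5% test.
- The rise occurs in TDF recipients only and equals the protocol's own 12 points (28% to 40%). Everyone else stays at 28%.
- No dropout, except where stated.

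**Formula.** With m visits and n men per group, SE = sqrt{[p1(1-p1) + p2(1-p2)] × [1 + (m-1)r] / (m n)}, z = |p2 - p1| / SE, and power ≈ Φ(z - 1.96).

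**1. The plan's own figure.** For 28% v 40%, n = 200, m = 3, r = 0.5: SE = sqrt(0.4416 × 0.6667 / 200) = 0.0384, z = 3.13, power 88% (82% at r = 0.7, 94% at r = 0.3). The protocol's claim of more than 80% is reproduced as a longitudinal figure without dropout.

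**2. Immediate v delayed under a TDF-only rise.** The immediate group averages (28 + 40)/2 = 34%, so the contrast is 6 points, half of 12. SE = sqrt(0.4260 × 0.6667 / 200) = 0.0377, z = 1.59, power 36% (31% at r = 0.7, 43% at r = 0.3).

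**3. TDF v placebo, immediate arms only, same three visits.** n = 100: SE = sqrt(0.4416 × 0.6667 / 100) = 0.0543, z = 2.21, power 60% (52-70%).

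**4. TDF v placebo, all men, shared 15 months on product.** n = 200, m = 5: SE = sqrt(0.4416 × 0.6 / 200) = 0.0364, z = 3.30, power 91% (83-97%).

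**5. A larger TDF-only rise of 20 points.** The immediate group averages (28 + 48)/2 = 38%, so immediate v delayed is 38% v 28%. SE = sqrt(0.4372 × 0.6667 / 200) = 0.0382, z = 2.62, power 75% (67-83%).

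**6. With 20% loss, r = 0.5.** Replacing n by 160, 80 and 160 in steps 2, 3 and 4 gives 30%, 51% and 84%.

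A pooled-variance version of the test moves these results by about one percentage point or less. Power was not computed for the before-and-after comparison or for the within-group trends in Section 10.6.

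**The case against.** The strongest reply is that the protocol does not ignore product.

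- Section 10.6 looks at behavior within TDF and within placebo and relates it to perceived assignment, which bears directly on the mechanism.
- Sections 10.1 and 10.2.1 can be read to cover the contrast.
- Section 10.5 makes immediate or delayed an adjustment factor, so the remaining treatment variable is naturally TDF versus placebo.
- The exact model and a perceived-by-actual table are matters for a statistical analysis plan, which is not shown.
- The pooled comparisons can be run without using the product codes.

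Much of this stands. A reader might infer that behavior is never analyzed by product; Section 10.6 shows otherwise. What survives is narrower. Two separate within-group trends are not a comparison between the groups, the general sentences name no contrast, and none of them changes what the self-unblinding subsection tells the safety review to examine. That text is a stated method aimed at the wrong contrast, not a detail left open.

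A reader might also infer that the bias would usually be missed. That holds for immediate versus delayed at rises near 12 points. At 20 points that comparison has 67-83% power, although its result still could not be attributed to self-unblinding. The other listed analyses were not evaluated.

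Setting 36% beside 91% is not like for like, because the second figure uses more visits and more men on product. Over the same nine months the fair figure is 60%. Nor does 91% apply to the safety reviews at 6, 12 and 18 months after study initiation. Enrollment runs over 24 months and delayed product starts at month 9, so no delayed participant can be on product at the first review.

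Finally, the consequences should not be inflated. HIV incidence is a secondary endpoint, few infections are expected, and the protocol nowhere claims that the blind held.

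**Conclusion.** The point holds in this form. The two comparisons specified in the self-unblinding subsection pool TDF with placebo, halve a TDF-only change in risk behavior, and cannot separate it from a general effect of taking tablets. No section states a between-group TDF versus placebo comparison of risk behavior.

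For a 12-point TDF-only rise, immediate versus delayed has about 36% power. TDF versus placebo has about 60% over the same visits in the immediate arms and about 91% at the final analysis. These figures rest on the assumed size of the rise, a correlation borrowed from the adherence section, two-sided testing and no dropout. The problem of attribution depends on none of them. The change is worth making because it is cheap and the protocol itself treats this bias as important.

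**What to change.** In the self-unblinding subsection and in Section 10.6, state that TDF versus placebo risk behavior while on product is the comparison that addresses self-unblinding. Use the longitudinal models already planned, adjusted for site and for immediate or delayed group, with all participants over the first 15 months on product. This follows the pooling Section 10.7 already uses for adherence. Add a table of perceived by actual assignment. Run both at the final analysis. Keep immediate versus delayed as the analysis of behavioral disinhibition, and do not present it as evidence about the blind.

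The cost is about two sentences, one further model and one table, all on data already collected. The small downside is at the safety reviews: before database lock only the statistician who holds the codes can run the comparison, and only on the limited on-product data then available.
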